### Study goal and hypotheses

This RCT will examine whether a home-based, individually tailored approach to AT provision can improve older adults’ independence and decrease their family caregivers’ perceived burden compared to customary care. We expect that older adults randomized to the experimental condition will have higher activity performance following the novel intervention than those assigned to customary care, and that family caregivers will report significantly reduced burden in their caregiver activities.

*Hypothesis 1*: Compared to AT users in the customary care group, AT users in the experimental group will perform daily activities more independently after completion of the intervention. Secondarily, AT users in the experimental group will also perform instrumental activities of daily living more independently following the intervention.

*Hypothesis 2*: Following the intervention, family caregivers in the experimental group will report a significantly reduced frequency of physical and psychological demands associated with problematic caregiving activities, compared with caregivers in the customary care group. Secondarily, family caregivers in the experimental group will experience a decrease in their overall perceived burden following the intervention.

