### Quantitative sample size

Sample size was calculated for the primary endpoint (22 weeks) for older adults and family caregivers separately and the largest sample size was selected. The sample size for the primary caregiver outcome measure (CATOM) was chosen to detect a 10 % decrease in perceived burden. This is consistent with the caregiver burden change noted in a prior trial using CATOM scores at baseline and after 16 weeks [31]. It indicates a one-level decrease on half of the items for the family caregivers (nearly always → frequently → sometimes → rarely → not at all). The primary older adults’ outcome measure is the SMAF. The sample size was chosen in order to detect an improvement of 9 % following the intervention. This value is intermediate between the minimal detectable difference and the change measured by administering the SMAF in a study examining the impact of a rehabilitation program on individuals with post-cerebral vascular accident [44, 45].

To determine an effect size, Cohen’s *D* was calculated using standard deviations from our prior study [31] and then transformed into Cohen’s *F* [46, 47]. As the effect size was smaller for the SMAF, we used this value to simulate various potential scenarios using G*Power 3.1.0.87. For these simulations we varied several variables including 1) effect size (0.13 to 0.15), 2) correlations among repeated measures (which previous data suggest will be moderate for pre-post intervention and strong between post intervention and long term follow up, e.g. 0.5 to 0.6), and 3) violations of sphericity (due to differences in variances over time, e.g., 0.6 to 0.9). The average of these sample sizes is 102. Based on approximately a 20 % dropout rate for the main trial endpoint (suggested by the prior study in which dropout occurred exclusively due to health related issues, which are common in this population), a sample of 120 dyads will be recruited (40 from each site).

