### Quantitative data analysis of primary and secondary outcome measures

Data will be entered by raters into SPSS statistics data editor (IBM SPSS Statistics) immediately after each evaluation session to decrease the likelihood of missing data. The use of multiple imputation will be explored to deal with any missing data, especially if a participant is unable to be assessed at one of the data collection time-points [48].

To ensure baseline similarity between groups, the experimental and control groups will be compared on socio-demographic and clinical variables with the use of *t*-tests for continuous data and Chi-square for nominal data. Descriptive statistics and histograms will be used to display differences between the groups. A repeated measures analysis of variance will be conducted to analyze dependent variable data, using a Greenhouse-Geisser correction to address issues with sphericity.

Scores for the primary outcome measures (SMAF and CATOM, items 1–14) will be compared between treatment groups over time using an intention-to-treat analysis. Intention-to-treat analysis dictates that all participants are included in the group to which they were allocated for purposes of analysis, whether or not they completed the intervention for that group. The same analysis will be applied to secondary outcome measures, which include the RNLI, CATOM (items 15–18), CBI, self-report FIM and hours of care provided by family caregivers. These secondary outcome analyses will be considered exploratory in view of the increased likelihood of Type I errors resulting from multiple statistical comparisons. Sensitivity analyses will be performed to compare the effect of the interventions on 1) caregiving spouses versus caregiving adult children, and 2) on participants receiving services at the different sites.

To test for changes in family caregiver burden due to the intervention, changes in older adults’ SMAF scores will be correlated with changes in their caregivers’ CATOM scores, using either a Pearson or Spearman correlation depending on the distribution of the data.

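### A supplementary SMAF–CATOM correlation is given the purpose of testing burden change caused by the intervention, which it cannot do; the randomised CATOM comparison that can do so is already planned

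*Protocol article*

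**What the plan says.** Hypothesis 2 (Study goal and hypotheses) is a between-group statement. It expects that "family caregivers in the experimental group will report a significantly reduced frequency of physical and psychological demands associated with problematic caregiving activities". The comparator is named explicitly: "compared with caregivers in the customary care group".

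The section Quantitative data analysis of primary and secondary outcome measures contains two analyses that bear on caregiver burden:

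- **Randomised comparison.** "A repeated measures analysis of variance will be conducted to analyze dependent variable data", with a Greenhouse-Geisser correction. Scores on SMAF and on CATOM items 1–14 "will be compared between treatment groups over time using an intention-to-treat analysis".
- **Correlation.** The last paragraph opens with a causal purpose, "To test for changes in family caregiver burden due to the intervention", and assigns this method to it: "changes in older adults’ SMAF scores will be correlated with changes in their caregivers’ CATOM scores". The choice of statistic is left open: "using either a Pearson or Spearman correlation depending on the distribution of the data".

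The correlation sentence names no treatment group, control contrast, time point, adjustment or mediation model. The section calls the secondary outcome analyses exploratory. The correlation, which uses the two primary measures, carries no such label.

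**The concern.** The stated question and the stated method do not match. Whether burden changed because of the intervention is a question about random assignment, and it needs a contrast between the arms. Correlating one dyad member's change with the other's supplies none.

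The document itself gives reasons to expect some association whatever the allocation:

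- The Background describes models in which the older adult's use of assistive technology alters the help the caregiver must give.
- Control dyads also receive equipment under customary care.
- The life changes form exists because events in either person's life could move the outcomes.
- SMAF is administered to the two members together, so the caregiver may contribute to both scores.

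What is at stake is interpretation. As worded, the plan has two analyses that can be read as testing burden due to the intervention, and only one of them does. Nothing in the text stops a significant correlation from being reported as an intervention effect beside a null randomised comparison.

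**Working it through.** The plan gives no figure for this analysis, so there is none to reproduce. The check is of what the correlation responds to.

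**Inputs**

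- Dyads: the protocol recruits 120 and expects about 20% dropout, so 120 × 0.8 = 96. A second set of runs used 102, from "The average of these sample sizes is 102" (Quantitative sample size).
- Assumed, because the document does not give them: two-sided 0.05; the within-arm correlation ρ of the two changes; the effects of the intervention on SMAF change (d_S) and CATOM change (d_C) in SD units; equal arms; normal changes with within-arm SD 1.

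**Step 1. What the pooled correlation measures.** With equal arms,

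r_pooled = (ρ + d_S·d_C/4) / √[(1 + d_S²/4)(1 + d_C²/4)].

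The intervention enters only through the product d_S·d_C and the variances. If there is no effect, r_pooled = ρ. If burden falls without a SMAF change (d_S = 0) and ρ = 0, then r_pooled = 0 however large d_C is. If the arms are analysed separately, each correlation is simply ρ and the intervention effect drops out altogether. Neither version tests it.

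**Step 2. No intervention effect on either outcome, 96 dyads.** By the Fisher approximation, power = Φ(z − 1.96) + Φ(−z − 1.96), where z = atanh(r)·√(N − 3) and √93 = 9.644.

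| ρ | atanh(ρ) | z | Probability significant | Simulated, 10,000 trials |
|---|---|---|---|---|
| 0.2 | 0.2027 | 1.955 | 50% | 50% |
| 0.3 | 0.3095 | 2.985 | 85% | 85% |
| 0.4 | 0.4236 | 4.086 | 98% | 98% |

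The between-arm CATOM test rejects in about 5% of the same simulated trials, as it should.

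**Step 3. A real effect that the correlation misses, 96 dyads.** Take 0.5 SD on both outcomes and ρ = 0. Then r_pooled = 0.0625/1.0625 = 0.059, z = 0.0589 × 9.644 = 0.57, and the probability of significance is 9%. A between-arm t-test on CATOM change has noncentrality 0.5 × √(96/4) = 2.45 and power 68%.

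**Step 4. Simulation with 102 dyads, 51 per arm, 4,000 trials per row.** A plus sign means that the two effects have the same sign, a minus sign that they have opposite signs.

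| Scenario | Pooled correlation significant | Experimental arm only | Between-arm CATOM test |
|---|---|---|---|
| No effect, ρ = 0.3 | 88% | 59% | 5.5% |
| No effect, ρ = 0.5 | over 99% | 97% | 4.3% |
| 0.6 SD on burden only, ρ = 0 | 4.9% | 5.5% | 85% |
| 0.6 SD on both (−), ρ = 0 | 14% | 5.8% | 85% |
| 0.6 SD on both (+), ρ = −0.09 | 4.7% | 10% | 85% |

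In the last row the pooled covariance is −0.09 + 0.36/4 = 0, so the two sources of association cancel.

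The correlation can therefore be significant with no intervention effect, and null with a real one.

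**The case against.** The strongest reply is that the plan already answers the burden question correctly. Hypothesis 2 is a between-group contrast, and the intention-to-treat comparison of CATOM items 1–14 tests it. The correlation comes after the primary, secondary and sensitivity analyses, is not named as primary, and played no part in the sample size. This stands, and it limits the point. A reader might infer from the last paragraph that the correlation is how the trial tests caregiver burden, or that no randomised comparison of burden is planned. The document does not support either reading.

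A second reply is that the percentages in Step 2 are the power to detect a correlation that was assumed to exist. This also stands. They are not the false-positive rate of the trial's burden test, and the correlation is a valid test of association. They become misleading only if the result is read in the way the sentence's stated purpose invites.

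A third reply is that a condensed article does not say whether the arms are pooled or separated. That is true, but it does not rescue the sentence, because neither version contrasts the arms. Nor is this a detail left to an analysis plan: the article states both the purpose and the statistic, and they do not fit each other.

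**Conclusion.** The point holds in a limited form. The last paragraph of the analysis section assigns a causal purpose to an analysis with no randomised contrast, and nothing elsewhere in the document corrects it. That conclusion rests on the wording alone. The sizes rest on assumptions: within-dyad correlations of 0.2 to 0.4 give about 50% to 98% significant results with no intervention effect, and a 0.5 SD effect on both outcomes with no within-arm correlation gives about 9%. The true correlation between SMAF change and CATOM change is not stated in the document.

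The primary comparison, the sample size and the test of Hypothesis 2 are unaffected. It would go too far to say that the trial's conclusion on caregiver burden rests on this correlation. The risk is a mislabelled supplementary result, so this is a moderate or minor correction.

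**What to change.** Reword the last paragraph of the analysis section to do two things:

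1. State that burden change due to the intervention is tested by the between-group comparison of CATOM items 1–14 already planned.
2. Describe the SMAF–CATOM correlation as an exploratory association between dyad members' changes, reported separately by arm and not used as evidence of an intervention effect.

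This changes wording only. It needs no new data, visits or participants.

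If the pathway from the older adult's function to caregiver burden is of interest, an exploratory mediation model that includes arm and the baseline SMAF and CATOM scores could be added. That is optional and costs a little more analysis work.

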### Quantitative data analysis for treatment fidelity

The percentage of intervention protocol items completed for each dyad in the experimental group will be calculated to determine treatment fidelity. These data will be supplemented with quantitative data retrieved from the adherence form, life change forms and chart reviews.

### Quantitative data analysis for intervention information

For both groups, descriptive statistics will be used to characterize therapists’ number, length, and total time of visits; the number, types, and costs of devices; and occupational therapists’ qualifications, years of practice, and years of experience working in this area. Exploratory post-hoc analysis will examine how these intervention elements may have contributed to the various results such as therapist differences, intensity of intervention, delay in receipt of equipment, and types of devices provided.

### Participants for the qualitative study

To obtain variation within our interview sample [49], participants will differ in terms of 1) type of family caregivers, e.g., spouses or adult children; 2) older adults’ baseline functional autonomy levels (based on SMAF scores); 3) type of AT provided; 4) research sites, and 5) experimental versus control group membership. Based on our previous research with this population and suggested sample sizes for such research [50], we expect to conduct interviews with 20 to 25 dyads (40–50 individual interviews). As a sub-sample of the larger study, interview participants will meet all of the inclusion criteria for the quantitative study described above. As part of the consent process, we will indicate that participants in the subsample may be asked to take part in two additional qualitative interviews.

### Qualitative measures and data collection

To better understand how the intervention was administered by therapists and experienced by older adults and their family caregivers, three systematic qualitative methods of data collection will be used. First, the registered occupational therapists providing the experimental intervention will keep a record of the interventions that they provide. The records will be reflective in nature and describe a) the content of the treatment session, b) elements of the intervention that seem to be working well, c) aspects that could be improved and d) general impressions. Second, therapists from each site, regardless of whether they administered care to the experimental or control group, will be invited to be interviewed individually to determine the process they used when providing AT. Third, qualitative interviews will be conducted with a purposeful selection of AT users and family caregivers, to refine emerging interpretation of the experience throughout the study. A member of the research team who was not involved in data collection or treatment administration will conduct these interviews. They will be scheduled following quantitative data collection at week 6 and at the end of the study.

### Qualitative data analysis

Qualitative interviews will be digitally recorded and transcribed verbatim. The transcripts will be reviewed while listening to the audio file to ensure accuracy. Each interview transcript and audio files will be labeled and stored in qualitative data analysis software (NVivo10) according to a) the participant’s pseudonym, b) the type of participant (occupational therapist, family caregiver or AT user), c) the group type (control or experimental), and d) its location (Montreal, Ottawa or Vancouver).

By repeatedly reviewing the data, we will develop ideas and interpretations about recurring, converging and contradictory patterns and will identify key concepts and themes along with illustrative examples [51]. Broad categories will be developed to organize and inductively code the raw data. Themes within and across participants are likely to emerge by means of this iterative process [50]. Examples from the themes will be retrieved and compared between and within field notes, participant observations, and interview transcripts. As the review progresses, data will be coded and re-coded to reflect emergent themes. “Negative cases” that do not fit with the emergent themes will be explored to develop tentative explanations for them. Ultimately, codes will be grouped into relevant themes, and they will be organized in a manner that is intended to promote understanding of how the experimental and control interventions were experienced.

Results from the treatment reflections and qualitative interviews will be compared with the quantitative results for older adults and their family caregivers to look for divergent and complementary findings. The results for each member of the dyad will be scrutinized separately, as will data for the dyads comprising the experimental group, especially when exploring interaction effects between older adults and family caregivers. Qualitative and quantitative data will also be compared for individual participants.

Given the previously demonstrated efficacy of AT in earlier RCT interventions [9, 31, 52, 53], no data monitoring committee (DMC) will be used. The final qualitative and quantitative trial dataset produced by the intervention will be managed by and accessible to study investigators, only. The dissemination of all findings and analysis will be through academic articles authored by the investigators that are published in refereed open access journals. Participants who express interest will receive a lay summary of the findings of the study.

## Discussion

As a society, we need all the empirical, methodological, and theoretical knowledge available to respond adequately to the problems faced by older adults, their family caregivers, and service providers with respect to the efficient use of assistive technology. This study will be the first parallel-group RCT to examine an AT intervention with emphasis on both the older adult with disabilities and his/her family caregiver. Providing evidence of the effectiveness of such an approach will encourage service providers and clinicians to move forward with AT recommendations that are more attuned to the needs of both members of the dyad. It is important to recognize the societal importance of responding to the needs of family caregivers who in many instances may be aging themselves. Resource limitations and social policies that promote aging in place also bolster the call for an adequate response to family caregivers’ needs. Positive findings will highlight the value of an approach to AT provision that is more inclusive of family caregivers and will set the stage for econometric studies assessing its cost-effectiveness.

The study is designed to evaluate the effectiveness of an AT intervention in real-life conditions. As such, the results are prone to be influenced by a host of factors including older adults’ and family caregivers’ clinical and socio-demographic characteristics, their home-related problematic activities, their home environment, the device types they are supplied, and the dynamics of the relationship between them. This places a premium on having sufficient power to control for the concomitant effects of those factors. However, this study has the advantage of being built on the results of a previous one, which did detect a clinically significant effect of the ATPUT intervention [31]. Moving from that study to this planned, parallel-group RCT is a logical step toward the next best evidence. The results from the planned study should be transferable and usable in real life.

Our design combines qualitative and quantitative methods and measures. Given the limited research on the relationship between caregiver burden and AT, the qualitative data will extend our knowledge in this area beyond the results of the quantitative portion of the research and will allow exploration of possible feelings of ambivalence toward assistive devices that have been reported in previous studies [54, 55]. The proposed research approach may serve to highlight ways of improving the way AT and AT education is provided in the community, and may suggest a model for assessing the effectiveness of other AT interventions. It may also advance the methodology of studying AT outcomes for AT users and caregivers.

## Ethics approval and consent to participate

The research protocol to be used in this study has been approved by the offices of research ethics boards of the participating sites: Institut Universitaire de Gériatrie de Montréal (reference 11-12-018), West Island Health and Social Services Center (no reference number), University of Ottawa (reference A09-11-02), Bruyère Continuing Care (reference M16-11-021), University of British Columbia – Providence Health Care Research Institute (reference H12-03195), and Simon Fraser University (reference 2011 s0346). All participants consented to be involved in the study.

## Consent for publication

Not applicable.

## Availability of data and materials

The dataset(s) supporting the conclusions of this article are available to the public and can be obtained by contacting the first author.

## Abbreviations

AT: assistive technology
ATPUT: Assistive Technology Provision, Updating and Tune-Up
CATOM: Caregiver Assistive Technology Outcome Measure
CBI: Caregiver Burden Inventory
EQ-5D: European Quality of Life
FIM: Functional Independence Measure
MoCA: Montreal Cognitive Assessment
RCT: randomized control trial
RNLI: Reintegration to Normal Living Index
SMAF: Functional Autonomy Measurement System
